# FINANCE AND INSURANCE

## Funding

The study is being funded from the CONBRIO (Collaborative Network for Bipolar Research to Improve Outcomes) Wellcome Trust Strategic Award and the NIHR Oxford Health Biomedical Research Centre. CONBRIO is a programme of translational research intended to transform the understanding and treatment of bipolar disorder.

## Insurance

The University has a specialist insurance policy in place which would operate in the event of any participant suffering harm as a result of their involvement in the research (Newline Underwriting Management Ltd, at Lloyd’s of London).

# PUBLICATION POLICY

The main results of the study will be published together in an appropriate journal and made available to participants via the Department of Psychiatry website. Additional results from the individual themes will be published in topic-specific journals.

# Appendix A: Participant pathway

**Visit 2- Randomisation**

- Check on adverse events

**Follow-up Call**

- Confirmation of willingness to continue in the study
- Eligibility check –adherence to rating scales
- Randomisation:

If eligible:

**Allocated nicardipine/placebo**

- Pre-treatment brain scans
- Provided with second e-Patch heart rate monitor
- Provided with portable blood pressure monitor
- Blood samples taken, weight, blood pressure, pulse and ECG repeated.
- Cognitive tests completed
- Post-treatment brain scans
- Device(s) returned.
- Checks for adverse events
- Informed Consent
- Eligibility assessment by using the MINI and completing a battery of cognitive tests
- Medical history and pregnancy test
- Weight, blood pressure and pulse recorded
- Baseline cognitive tasks and ECG completed
- iPad and activity monitor set-up and provided
- Weekly and daily self-reporting started.
- Blood samples taken
- Provided with e-Patch heart rate monitor and sleep diary for a 72-hour period prior to randomisation

**4 weeks**

Carry the GeneActiv wrist worn activity monitor and complete questionnaires and cognitive tasks on an iPad - daily

True Colours ratings of mood –weekly

# Appendix B: Schedule of Procedures

| Attendance number | **1** | **2** | **3** | **4** |
| --- | --- | --- | --- | --- |
| Timeline (days) | **0** | **14** | **28** |  |
| Window (days) |  | **±2** | **±2** |  |
| Informed consent | ✓ |  |  |  |
| Demographics | ✓ |  |  |  |
| Diagnosis (MINI) | ✓ |  |  |  |
| Medical history | ✓ |  |  |  |
| Physical examination | ✓ | ✓ |  |  |
| ECG | ✓ |  | ✓ |  |
| Vital signs and BMI | ✓ | ✓ |  |  |
| Eligibility assessment | ✓ | ✓ |  |  |
| Follow-up call |  |  |  | ✓ |
| Personality disorder screen | ✓ |  |  |  |
| ADHD screen | ✓ |  |  |  |
|  |  |  |  |  |
| Neuropsychological tests | ✓ |  | ✓ |  |
| Randomisation |  | ✓ |  |  |
| True Colours | **✓** Weekly | | |  |
| PANAS | **✓** Daily | | |  |
| Cognitive tests | **✓** Daily | | |  |
| Carry activity monitor | **✓** Daily (with regular data downloads) | | |  |
| Concomitant medications | ✓ | ✓ | ✓ |  |
| Dispensing study drugs and pill count |  | ✓ | ✓ |  |
| Adverse Event check |  | ✓ | ✓ | ✓ |
| MEG |  | ✓* | ✓ |  |
| MRI |  | ✓* | ✓ |  |
| Sleep questionnaire | ✓ | ✓ | ✓ |  |
| Sleep Diary card commenced | ✓ | ✓ |  |  |
| Sleep Diary card completed & returned |  |  | ✓ |  |
| ePatch** | ✓ | ✓ |  |  |
| Portable blood pressure monitor*** |  | ✓ |  |  |
| Blood tests | ✓ |  | ✓ |  |
| Devices returned |  |  | ✓ |  |

- *MEG and MRI scan prior to taking any study medication.
- ** Wear for 72 hours
- *** Participants to record blood pressure once daily throughout two-week randomisation phase

# Appendix C: SAE Reporting Flow Chart

**Adverse event**

**Adverse Event**

**No further action**

**Related to IMP?**

**Serious? (See box)**

**Expedited report to REC and Sponsor within:
 - 7 days if fatal/life-threatening, - 15 days if not**

**Yellow card system report**

**Ongoing Safety Review
by Steering Committee**

**Adverse Reaction**

**Serious Adverse Event**: any untoward medical occurrence that:

- results in death
- is life-threatening
- requires inpatient hospitalisation or prolongation of existing hospitalisation
- results in persistent or significant disability/incapacity
- consists of a congenital anomaly or birth defect.

Other ‘important medical events’ may also be considered serious if they jeopardise the participant or require an intervention to prevent

**Timeframe:** Must be reported to Research Team within 24 hours of becoming aware of SAE

**Inform Investigators**

**SUSAR**

**Expected?
(See SmPC)**

**Serious Adverse Reaction**

**Serious Adverse Event**

**Related to IMP?**

**Consistent with SmPC?**

# Appendix D: Rating scales

**Rating Scales**

Weekly mood ratings for the study will be captured on four scales, the Quick Inventory of Depressive Symptomatology (QIDS-SR_16_), the Altman Self-Rating Mania Scale (ASRM), the Generalised Anxiety Disorder Questionnaire (GAD-7) and the Quality of Life questionnaire (EQ-5D).

*QIDS-SR_16_*: The QIDS-SR_16_ is a 16-item self-report questionnaire that covers 9 key symptoms of depression (Rush, 2003). The scale is designed to assess both severity of depression and change in depressive symptoms over time.

Participants are instructed to score each item according to the description that best describes how they have been over the past 7 days. Each of the symptoms is scored on a 4-point scale (0 – 3) giving a maximum score of 27.

*ASRM:* The ASRM is a 5-item self-report questionnaire that assesses severity of and change in manic symptoms (Altman 1997).

Participants are instructed to score each item according to the description that best describes how they have been over the past 7 days. Each of the symptoms is scored on a 5-point scale (0 – 4) giving a maximum score of 20.

*GAD-7:* The GAD-7 is a 7-item questionnaire that assesses the frequency of anxious thoughts and behaviours (Spitzer et al., 2006).

Participants are instructed to score each item according to the description that best describes how they have been over the past 7 days. Each of the symptoms is scored on a 4-point scale (0 – 3) giving a maximum score of 21.

*EQ-5D*: The EQ-5D is a general health questionnaire assessing mobility, activity, self-care, the presence of pain or discomfort and anxiety or depression, and overall health state.

Participants are instructed to indicate whether they have no problems, some problems or are significantly affected by the above categories over the past 7 days. They are also asked to indicate on a scale their health state from 0 – worst imaginable state to 100 – best imaginable state.

**PANAS**

PANAS (Thompson, 2007) will be used to measure day-to-day mood variations which will be used as a covariate in the analysis of the daily cognitive tasks. Participants will be prompted to rate the extent to which 10 mood descriptors best describe their mood over that day. The ten descriptors are upset, hostile, alert, ashamed, inspired, nervous, determined, attentive, afraid, and active. Each is rated on a 5-point scale from never to always.

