## Study themes

The main focus of OxCaMS is the effect of nicardipine on variability in cognitive function as measured using daily cognitive tasks.

We will also explore the impact of nicardipine on, behaviour (including activity levels and sleep patterns), neural activity and circadian rhythms. Exploration of the effects of LTCC antagonists on these parameters and the correlation between these effects form a secondary focus for the study.

-**Regular cognitive tasks**. Brief cognitive tasks will be presented daily to participants on an iPad. These tasks will explore aspects of attention, reinforcement learning, working memory and risk sensitivity and will take around 10 minutes to complete each day. These paradigms are already being used in a number of other studies in healthy volunteers with mood instability (http://conbrio.psych.ox.ac.uk/comet).

-**Actigraphy**. Participants will be given a wrist mounted actigraph to wear for the duration of the study. In addition to movement the actigraph also collects data on ambient temperature and light. This will allow us to monitor movement and sleep with a high degree of accuracy.

-**Functional magnetic resonance imaging (fMRI).** Resting state and task-related functional imaging will be performed. Arterial spin labelling (ASL) sequences will also be performed. ASL is a non-invasive means of quantifying tissue perfusion (Petcharunpaisan 2010).

-**Magentoencephalography (MEG).** Resting state and task-related imaging will be performed.

- **Blood samples for genotyping** for the major BD-associated allele in *CACNA1C* (rs1006737). Blood samples will also be used to measure leucocyte calcium channel gene expression and studies of calcium signalling.

- **Heart rate variability** will be measured prior to and during the randomised phase using an e-Patch device [41]. This is an unobtrusive monitor, which provides a 72-hour heart rhythm trace. Heart rate variability is of interest because of the cardiovascular effects of nicardipine. (Bassett 2015).

Mood instability: this will be measured using root mean square of the successive differences (RMSSD). This is a standardised measure of instability that has been used in a number of studies

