Participant will also be asked to complete daily and weekly measures of mood in order to allow us to control for any changes is mood as we are wanting to explore the direct effect of calcium channel antagonism unconfounded by mood. Daily mood will be recorded using the short form of the positive and negative symptom scale (PANAS [37]) delivered on an iPad. The PANAS 10 item is a self-report scale which is widely used in psychiatric research. Weekly mood measures will be completed using the True Colours system ([www.truecolours.nhs.uk](http://www.truecolours.nhs.uk)). True colours is a mood monitoring platform developed in Oxford which is uses validated clinical scales to assess depression (quick inventory of depressive symptoms) and mania (Altman mania rating scale [39]).

All participants will have a two-week period of participation prior to randomisation. This will allow us to assess the stability of their cognitive function and collect baseline mood, sleep and activity data.

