# OBJECTIVES AND OUTCOME MEASURES/ENDPOINTS

| **Objectives** | **Outcome Measures/Endpoints** |
| --- | --- |
| Primary objective:   - To compare the effects of nicardipine and placebo on measures of cognitive instability.   . | Primary outcome measure:   - Cross sectional and longitudinal assessments of cognition |
| Secondary objective:   - To compare the effects of nicardipine and placebo on variability in neural dynamics during MRI and MEG scans. This will include scans during resting state and whilst performing neuropsychological tasks. - To explore the effects of nicardipine on physical activity and sleep. - To develop a profile of calcium channel expression and calcium signalling with and without nicardipine treatment - Heart rate variability - Mood instability | Secondary outcome measure:   - Blood oxygen level dependent signal during rest and during cognitive testing; induced and evoked field activity - Activity monitor measurements:   2a. Actigraphy data from a maximum of two wearable units, allowing analysis of indices of:   1. Frequency and amplitude of movements during daytime activity   ii. Categorisation of activity types.   1. Duration, timing, and quality of sleep.   2b. Sleep quality indicator questionnaire (SCI; self-report sleep measure (Espie, 2014)).   - Measure effects of nicardipine on leucocyte calcium channel expression and calcium signalling - Change in R-R interval variability - Change in mood instability using root mean square of the successive differences (RMSSD) |

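### Daily PANAS mood recorded after randomisation is made a covariate for the daily cognitive tasks, so the main comparison may be conditioned on an effect of the drug

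*Protocol*

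**What the plan says.** Appendix D (Rating scales, PANAS) states that the scale "will be used to measure day-to-day mood variations which will be used as a covariate in the analysis of the daily cognitive tasks". Section 4.2 (Study themes) gives the reason: mood is collected to "control for any changes is mood as we are wanting to explore the direct effect of calcium channel antagonism unconfounded by mood".

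The same section places those tasks at the centre of the study: "The main focus of OxCaMS is the effect of nicardipine on variability in cognitive function as measured using daily cognitive tasks". Section 5 gives the primary objective with no restriction to an effect net of mood: "To compare the effects of nicardipine and placebo on measures of cognitive instability". Section 5 also lists change in mood instability, measured by RMSSD, as a secondary outcome.

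Section 6.3 and the schedule in Appendix B show that the questionnaires and daily tasks run on through the randomised phase. Section 11.1 (Description of Statistical Methods) says only that the cognitive data will be correlated with the True Colours and PANAS data. It names neither an unadjusted comparison nor one adjusted for baseline mood.

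**The concern.** Allocation is randomised, so mood recorded afterwards cannot confound the drug comparison. A systematic difference in mood between the arms after allocation would be a result of treatment. The protocol allows for this, since it studies mood instability as an outcome. The same construct therefore serves both as something the drug may change and as a nuisance to be removed.

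If nicardipine changes mood, two things follow. First, the adjusted estimate leaves out whatever part of the cognitive effect runs through mood, and so stops answering the objective in section 5. Second, it isolates a direct effect only if mood and cognition share no unadjusted cause. Section 4.1 makes that doubtful: it links mood instability to sleep problems and to impaired cognition, and sleep is another outcome of this trial. With such a shared cause, the adjusted comparison can show a drug effect where none exists or hide a real one.

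**Working it through.** **No plan figure to reproduce.** The protocol gives no effect size, SD or expected drug effect on PANAS. Only the arm size (20 per arm, section 11.1) comes from the document. All other inputs are assumptions in SD units.

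**1. Mean-level cognitive endpoint, true drug effect zero.** Let T be treatment (0/1), M mood after randomisation, Y cognition and U an unmeasured shared cause:

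- M = aT + uU + noise
- Y = uU + noise
- within-arm SD of M and of Y = 1

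The within-arm slope of Y on M is u². The coefficient of T adjusted for M is therefore 0 - a·u².

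- a = 0.5, u = 0.5: -0.5 × 0.25 = -0.125 SD
- a = 0.5, u = 0.7: -0.5 × 0.49 = -0.245 SD

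The standard error is √[(1 - u⁴) × (2/20) × (1 + a²/4)].

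- u = 0.5: √(0.9375 × 0.1 × 1.0625) = 0.316; bias/SE = 0.40; type I error 6.7% (noncentral t, 37 df)
- u = 0.7: √(0.7599 × 0.1 × 1.0625) = 0.284; bias/SE = 0.86; type I error 13.4%

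Repeated simulations agree: bias of about -0.12 to -0.25 SD and type I error of about 6% to 15%, against about 0 and 5% unadjusted. A larger assumed shift (a = 0.8, u = 0.7) gives -0.8 × 0.49 = -0.39 SD and about 25%.

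**2. Effect running partly through mood, no shared cause.** Take a total effect of 1.05 SD, which has about 90% power unadjusted with 20 per arm. With a mood shift of 0.5 and a mood-cognition slope of 0.5, the adjusted estimate is 1.05 - 0.5 × 0.5 = 0.80 SD, and power falls to about 78%. This is a change of estimand: 0.80 is the correct direct effect, but not the effect that section 5 asks for.

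**3. No drug effect on mood (a = 0).** The adjusted estimate is unbiased. Power is somewhat higher, at 91% to 97% against 89% to 90% unadjusted.

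**4. Variability endpoint.** The stated objective is instability, so the check was repeated with 14 daily values per person, zero true cognitive effect and loadings of 0.5 to 0.7.

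- A constant 0.5 SD mood shift gives a bias of about 0, with type I error near 5%. A constant drops out of successive differences.
- If the drug reduces mood SD by 20% to 50% and cognition is residualised on daily mood, the bias is small (at most about 0.15 SD in absolute size) and type I error is 5% to 7%.
- With the same reductions and each person's mood RMSSD as the covariate, the bias is about 0.05 to 0.6 SD, with type I error up to about 19%.

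For the instability objective, the size therefore depends on whether the drug alters mood variability and on how the covariate enters the model. The protocol settles neither.

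**The case against.** The strongest defence is that the adjustment is deliberate. Section 4.2 wants a direct effect, and section 4.1 says that the aim is not efficacy but to use the drug to explore the role of calcium channels. On that aim, removing an effect that acts wholly through mood is correct. This stands: such a loss should not be called bias. But section 5 does not state a direct-effect objective, and simple covariate adjustment needs an assumption of no shared cause that the protocol does not discuss.

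The defence also limits how far the point can be taken. A reader might infer any of the following, and the document does not support them:

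- *The whole primary analysis is affected.* Appendix D covers the daily tasks only. The primary outcome also includes the visit-based battery (Appendix E), for which no PANAS covariate is stated. An unadjusted comparison is not ruled out; it is simply not named.
- *The mean-level figures apply to the stated objective.* They do not. A constant mood shift leaves a variability measure essentially untouched.
- *Later mood is purely a consequence of treatment.* It also reflects pre-existing mood instability, which is the entry criterion, and ordinary daily variation.
- *The covariate contains the outcome, because alert and attentive are PANAS descriptors.* Two of ten self-report items are not task performance. There is no need to remove items from an established short form.

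**Conclusion.** The point holds in conditional form. As written, the protocol adjusts the comparison on its main-focus tasks for a variable that is measured after randomisation and that it also studies as a treatment outcome. If nicardipine changes mood, the result no longer answers section 5, and it is a valid direct effect only without unadjusted shared causes of mood and cognition.

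It would go too far to say that the trial loses the protection of randomisation outright, because that requires a drug effect on mood and the protocol gives no expected effect on PANAS. Whether there is one is a question the trial itself asks, so the main comparison should not depend on the answer.

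The size is illustrative only: about -0.12 to -0.25 SD and 6% to 15% type I error for a mean-level endpoint under the stated assumptions. For an instability endpoint it ranges from about none to material, depending on the effect on mood variability and on the form of the covariate. This should be fixed, but it is not a fatal flaw.

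**What to change.** In Appendix D and section 4.2, state that the primary comparison of nicardipine with placebo on the daily cognitive tasks is not adjusted for mood collected after randomisation. If a mood covariate is wanted, use only PANAS level or instability from the two-week pre-randomisation phase.

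Keep the model with post-randomisation PANAS as a labelled secondary or exploratory mediation analysis. State its assumption that mood and cognition have no unmeasured common cause, and specify how mood enters the model.

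The cost is wording in the protocol and the matching text in the SAP. The pre-randomisation PANAS data are already collected, and the mechanistic question is kept.

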# Appendix E: Theme 2 Cognitive tests and neural dynamics

**Neuropsychological tests at baseline and in week 4.**

At the screening and scanning appointments, participants will be asked to complete a battery of cognitive tasks related to emotional processing, working memory, attention and behavioural inhibition which participants complete on a computer. In addition they will be tested for IQ.

**Daily cognitive tasks**

Participants will be provided with an iPad on which they will complete daily cognitive tasks via the True Colours System.

Thorough details of the cognitive tasks will be provided in the participant information sheet.

The tasks should not take longer than 10 minutes to complete and will tap into working memory, learning and attention processes.

**Scans**

Both scans will record resting state activity and brain activity in response to cognitive tasks. MRI and MEG scans will take place at the Oxford centre for Human Brain Activity (OHBA) at the Department of Psychiatry Warneford Hospital Site.

**MRI**

Once contraindications to magnetic resonance imaging are excluded by use of the facility’s screening forms, the risks of undergoing a scan are minimal. A trained scanner operator or radiographer will go through a list of possible risks with the participant before scanning. The MRI scanner consists of a large powerful magnet. Magnetic resonance imaging uses no ionising radiation. There are, however, potential hazards associated with MRI and the scanning of participants including the presence of surgical implants, participants’ clothing, jewellery (such as body piercings) bodily habitus, or medical conditions. A comprehensive list of potential risks has been compiled, and the participant should be checked against this by the operator, prior to entering the controlled areas of the MRI scanners. During the actual scanning procedure, the scanner produces loud banging noises and the participant will be given suitable hearing protection (earplugs and protective headphones). There is a small mirror that will allow them to see out of the scanner. During the experiment, the participant will be able to communicate with the operator in the control room. In addition, they will be given a call button, which allows them to alert the operator at any time. People with a history of claustrophobia may be excluded from participation in the study. All participants will still be introduced carefully to the scanner and allowed to leave at any stage, should they wish to do so. Once in the scanner, participants will be able to indicate immediately if they wish the scanning to cease by pressing a call button in their hands.

*MRI measurements*

- T1- weighted image: Structural scan to provide anatomical information
- T2-weighted image: FLAIR scan to provide information about white matter hyperintensities (WMH) lesions
- Diffusion tensor imaging (DTI): scan to provide information about white matter properties and fibre tracts
- Resting state scan: eyes open, participants will be asked to stay in the scanner and think of nothing in particular
- Task based activation scan

.

**MEG**

MEG is a silent, non-invasive brain imaging technique that measures the magnetic fields produced by nerve cells. During the MEG scanning eye movements will be tracked.

The MEG system contains very sensitive detectors arranged around a helmet shaped hollow. Brain activity is measured from a participant as they sit with their head inside this hollow. Because the magnetic signals produced by brain activity are tiny compared to those produced by the earth and electrical equipment, the scanner is in a specially built room that keeps out magnetic fields from the environment. MEG does not generate any magnetic fields and does not involve any ionising radiation. There are no known risks associated with MEG.

MEG is a very sensitive technique and measurements can be affected by metal in the room. Participants will be asked to remove metallic objects that they are carrying or wearing, for example, jewellery, body piercings, removable dental braces and clothing with metal parts. Participants with metal in their body (e.g. plates, dental work, pacemakers) will discuss this with the researcher in advance.

Those who wear glasses will inform the researcher in advance and they may be given special non-metallic glasses to wear. In some cases it may not be possible to scan the participant.

Before the MEG scan, the researcher will attach sensors to the participant’s wrists to measure their heartbeat and around their eyes to measure eye movements. The researcher will also place small coils on the participant’s forehead and above their ears to record their head position in the scanner. Participants can ask the researcher to stop at any time.

*MEG measurements*

Resting state scan

Task based activation scan

